### 3 STUDY DESIGN

#### 3.1 CLINICAL TRIAL FLOW CHART

[figure not shown]

### 4 SPONSOR

Not applicable

### 5 POPULATION

#### 5.1 Inclusion Criteria

Inclusion criteria for all the participants:

- 18 – 85 years old.
- Individuals without a prior history of cancer.
- Individuals with a plasma sample that was collected before initial screening tests and passed quality control (QC).
- Individuals who provided informed consent.

**Inclusion criteria for cancer arm participants:**

- Individuals who were pathologically confirmed with gastric adenocarcinomas by biopsies without concomitant malignancies and received curative surgeries for gastric cancer.

**Inclusion criteria for non-cancer arm participants:**

- Individuals who showed no signs of cancers based on routine physical examinations, including blood tests, ultrasound and CT, and no sign of gastric cancer from gastric cancer-specific screening tests.

## **5.2 Exclusion Criteria**

**Exclusion criteria for all the participants:**

- Individuals who withdrew informed consent.
- Individuals whose sequencing data failed QC.

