| Number of Sites    | Single site                                                                                                                                                                                                                                                                                                                                                                                                                                                                                                                                                                                                                     |
| Rationale          | Gastric cancer remains as one of the leading causes of death worldwide. Detecting gastric cancer earlier is vital for managing the disease effectively, improvement of survival rates and reduction of morbidity. Blood-based liquid biopsy has emerged as a promising technology for the early detection of multiple types of cancer, which can complement traditional cancer screening methods in a non-invasive manner. We developed a novel liquid biopsy assay using multi-dimensional cell-free DNA (cfDNA) features from whole genomic sequencing (WGS) data for the detection of gastric cancer at early stages.        |
| Study Design       | A single-center prospective observational study will be used to develop and valid the gastric cancer early detection study. The study is divided into two phases. The first phase of the study will enroll ~250 participants, including ~100 stage I-II gastric cancer patients and ~150 non-cancer individuals, over a period of 8 months. The cfDNA profiles of these participants will be used to develop a multi-layer machine learning model for identifying cancer presences. The second phase of the study will enroll ~125 participants over a period of 4 months to validate the performance of the cfDNA-based assay. |

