|--------------------|------------------------------------------------------------------------------------------------------------------------------------------------------------------------------------------------------------------------------------------------------------------------------------------------------------------------------------------------------------------------------------------------------------------------------------------------------------------------------------------------------------------------------------------------------------------------------------------------------------------------------------------------------------------------------------------------------------------------------------------------------------------------------------------------------------------------------------------------------------------------------------------------------------------------------------------------------------------------------------------|
|                    | Second phase: ~50 stage I-II gastric cancer patients, ~75 non-cancer individuals.                                                                                                                                                                                                                                                                                                                                                                                                                                                                                                                                                                                                                                                                                                                                                                                                                                                                                                        |

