## **2 STUDY OBJECTIVES**

### **2.1 Primary Objectives (Primary Outcomes)**

1st Phase – Assay development and preliminary validation:

- Utilize the data collected in this phase to comprehensively profile cfDNA characteristics.
- Develop a classification model to distinguish gastric cancer patients from non-cancer individuals.
- Conduct five-fold cross validations to assess the assay's efficacy and calculate the AUROC metric for binary classification.

2nd Phase – Assay validation:

- Use the assay developed in the 1st phase to predict the cancer presences in the participants enrolled in this phase and calculate the AUROC metric for the predictions.

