## **2.2 Secondary Objectives (Secondary Outcomes)**

1st Phase – Assay development and preliminary validation:

- Establish an appropriate threshold that maximize Youden's index from cross validations.
- Calculate the sensitivity and specificity of the assay at this threshold.

2nd Phase – Assay validation:

- Calculate the sensitivity and specificity of the assay at the predefined threshold from the 1st phase.

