### **7.2 Preliminary assessment and blood sample collection:**

After expressing interest or being approached for the study, participants will undergo a thorough assessment based on a predefined set of Inclusion and Exclusion criteria. This assessment ensures that only those individuals who meet the study's specific requirements and standards will be enrolled. A blood sample from each eligible participant will be collected following standard procedures.

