### **7.4 Sample processing:**

Plasma will be isolated from blood samples within 4 hours of collection and then stored at 4°C.

cfDNA will be extracted from plasma within 72 hours and stored at -80°C for later whole-genome sequencing (WGS). cfDNA profiles will be generated from WGS data using in-house analyzing pipelines.

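### QC failure, an outcome of the assay, is written as an eligibility rule, so Phase 2 accuracy is conditional on a valid result without saying so

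*Protocol*

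**What the plan says.** Section 5.2 of the protocol, repeated in the synopsis, lists among the exclusions for all participants "Individuals whose sequencing data failed QC". Section 5.1, also repeated in the synopsis, requires "Individuals with a plasma sample that was collected before initial screening tests and passed quality control (QC". Neither rule is limited to one arm or one phase, so both apply to the Phase 2 validation.

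Section 7.2 (under heading 8, Enrollment) has participants assessed against the criteria first and sampled afterwards: "A blood sample from each eligible participant will be collected following standard procedures". Section 7.4 places sequencing later still: "cfDNA will be extracted from plasma within 72 hours and stored at -80°C for later whole-genome sequencing (WGS".

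For Phase 2, section 2.1 asks the team to predict cancer presence in those enrolled in that phase and to "calculate the AUROC metric for the predictions". Section 2.2 adds: "Calculate the sensitivity and specificity of the assay at the predefined threshold". The synopsis gives the Phase 2 size as "Second phase: ~50 stage I-II gastric cancer patients, ~75 non-cancer individuals".

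The protocol states no QC thresholds, no expected failure rate and no rule for counting a sample that gives no result.

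**The concern.** Whether a sample yields usable sequencing data is part of how the assay performs. A rule that makes a failed sample a ground for exclusion takes that person out of the denominator of every accuracy measure. What remains is how well the assay separates the arms when it works. Section 1.1 motivates the assay as a tool for regular screening, and there a failed test detects no cancer and clears nobody.

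The Phase 2 figures could therefore be read as performance in all sampled stage I/II patients and non-cancer individuals when they cover only a subset. A confidence interval around the evaluable-sample estimate would not show the difference, because the lost samples are not in it.

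The rule is stated in the protocol, so this is not a detail left to the SAP. An SAP can define analysis sets among participants, but it starts from the protocol's definition of who is eligible.

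**Working it through.** **Timing.**

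1. Section 7.2: criteria are assessed, and then eligible people are sampled.
2. Section 7.4: plasma is isolated, cfDNA is extracted and stored, and sequencing follows later.
3. Section 5.2: failed sequencing QC excludes. The information for this rule arises only at the end of step 2, so it cannot be applied in step 1.
4. Section 5.1: plasma QC needs plasma, which under section 7.4 comes from the blood drawn after step 1. The same conflict of order applies.
5. Section 2.1: the Phase 2 predictions are meant for those enrolled in that phase. Someone enrolled under section 7.2 whose sequencing fails belongs to that group, yet section 5.2 removes them.

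**Inputs.** From the synopsis: Phase 2 has about 50 cancer and 75 non-cancer participants (50 + 75 = 125, which agrees with the stated total). The protocol gives no target accuracy and no failure rate, so there is no plan figure to reproduce. Assumed for illustration: sensitivity 0.80, specificity 0.90 and AUROC 0.90 among evaluable samples, and failure rate f of 2%, 5% or 10%, equal in both arms.

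**Sensitivity and specificity among everyone sampled, failures counted as incorrect.** Value = evaluable value × (1-f).

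| f | Sensitivity | Specificity |
|---|---|---|
| 2% | 0.80 × 0.98 = 0.784 | 0.90 × 0.98 = 0.882 |
| 5% | 0.80 × 0.95 = 0.760 | 0.90 × 0.95 = 0.855 |
| 10% | 0.80 × 0.90 = 0.720 | 0.90 × 0.90 = 0.810 |

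Against this target the evaluable figure is too high by the factor 1/(1-f), which is 1/0.95 = 1.053 at 5%.

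**Accuracy had the failed samples given a result.** The bias is the evaluable sensitivity minus [0.80(1-f) + s·f], where s is the sensitivity the failed cases would have shown. At f = 10%:

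- s = 0.40: 0.80 - 0.76 = +4.0 points (overstated)
- s = 0.80: 0.80 - 0.80 = 0
- s = 0.95: 0.80 - 0.815 = -1.5 points (understated)

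For this target the sign is not fixed.

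**AUROC.** A sample without a score has no rank, so a convention is needed. With f = 5% in each arm, (1-f)² = 0.9025 of case-control pairs are fully scored and 0.0975 are not.

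- Unscored pairs at chance: 0.90 × 0.9025 + 0.5 × 0.0975 = 0.861
- Unscored pairs all wrong: 0.90 × 0.9025 = 0.812
- Unscored pairs all right: 0.90 × 0.9025 + 0.0975 = 0.910

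The result lies below or above 0.90 according to the convention.

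**Scale.** The 95% half-width is 1.96 × √(0.8 × 0.2/50) = 0.111 for sensitivity and 1.96 × √(0.9 × 0.1/75) = 0.068 for specificity. At f = 5% the expected failures are 0.05 × 50 = 2.5 cancer and 0.05 × 75 = 3.75 non-cancer samples. If the planned sizes mean evaluable samples, 50/0.95 and 75/0.95 require 53 and 79 people to be sampled. The protocol does not say which meaning is intended.

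**The case against.** Accuracy given a valid result is a legitimate target for an assay-development study, especially as section 11 rules out diagnostic use of the results. This stands, and it is why the evaluable-sample analysis should be kept. The protocol, however, does not name that as its target.

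Section 5.2 also lists withdrawal of consent, which happens after entry. The list therefore mixes entry criteria with analysis-set exclusions, and the defect can be called one of labelling. That is fair, but whatever the label, the effect on the Phase 2 denominators is the same.

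Failure tables and supplementary analyses commonly sit in an SAP, which is not at hand. This stands for table layouts. It does not cover a protocol rule that puts these people outside the study population.

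Plasma QC concerns the specimen and sequencing QC concerns the assay output, so the two are not the same thing. This also stands, and sequencing QC is the clearer case. In Phase 1, samples without usable data cannot train a model, so the point bears on Phase 2.

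The shift is modest: at 2% to 5% failure, sensitivity moves by 1.6 to 4 points, against a half-width of about 11.

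The documents do not support three stronger readings that a reader might infer:

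- **All three measures are overstated.** Only sensitivity and specificity are, and only against everyone sampled with failures counted as incorrect. For accuracy given a valid result, no bias arises if failure is unrelated to cfDNA signal, and it may go either way if it is related. AUROC has no fixed direction.
- **Failures are quietly replaced until the planned arm sizes are reached.** No section describes replacement or says that failures will go unreported. They might simply reduce the sample.
- **Failure is more common in one arm.** The protocol gives nothing on failure by arm. It is a reason to report by arm and cannot be taken as a finding.

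**Conclusion.** The point holds in this limited form. The QC conditions are applied as eligibility rules although their results come after eligibility is settled, and they make all three Phase 2 measures conditional on a valid result without the protocol saying so.

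The firm quantitative statement is the factor 1/(1-f) for sensitivity and specificity, relative to everyone sampled with a failed test counted as incorrect. At the assumed 80%/90% and f = 5%, this is a fall of 4.0 and 4.5 points. The failure rate and the accuracy values are assumptions, so the actual size is unknown and would be zero if no sample failed. No direction is claimed for AUROC. The estimates may be optimistic for intended use, which is reason enough for a cheap correction but does not invalidate the study.

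**What to change.** For Phase 2:

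- Remove the plasma and sequencing QC conditions from sections 5.1 and 5.2 and the synopsis, and define QC failure as an outcome of the index test.
- Keep every consented, sampled participant with an established arm in the Phase 2 set, and say whether the planned arm sizes count sampled or evaluable participants.
- Report the number and rate of QC failures by arm, descriptively. With an expected 2 to 4 failures per arm at 5%, a significance test would have little power and a null result could falsely reassure.
- Give sensitivity and specificity twice: on evaluable samples, and with failures counted as incorrect (not detected in the cancer arm, not correctly negative in the non-cancer arm). Fix that convention in advance.
- State that AUROC is conditional on a valid result.

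Phase 1 model training may stay restricted to usable data.

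The cost is revised wording, one extra table and possibly slightly lower headline accuracy. No additional sampling is needed unless the arm sizes are declared to be evaluable counts.

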**Exclusion criteria for cancer arm participants:**

- Individuals who were pathologically confirmed with stage III/IV gastric cancer.

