| Primary Outcomes   | The area under the receiver operator characteristic curve (AUROC) metric for differentiating stage I/II gastric cancer patients and non-cancer individuals using the cfDNA-based assay.                                                                                                                                                                                                                                                                                                                                                                                                                                         |
| Secondary Outcomes | The sensitivity and specificity for differentiating stage I/II gastric cancer patients and non-cancer individuals using the cfDNA-based assay.                                                                                                                                                                                                                                                                                                                                                                                                                                                                                  |
| Interventions      | Not applicable                                                                                                                                                                                                                                                                                                                                                                                                                                                                                                                                                                                                                  |

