| Procedure          | This prospective study collects blood samples from participants with a new diagnosis of cancer (cancer arm) and from participants who do not have a diagnosis of cancer (non-cancer arm) to develop and validate the cfDNA-based assay for the early detection of gastric cancer.                                                                                                                                                                                                                                                                                                                                                                                                                                                                                                                                                                                                                                                                                                        |
| Inclusion Criteria | 
Inclusion criteria for all the participants:
 
 
• 18 – 85 years old.
 
• Individuals without a prior history of cancer.
 
• Individuals with a plasma sample that was collected before initial screening tests and passed quality control (QC).
 
• Individuals who provided informed consent.
 
 
Inclusion criteria for cancer arm participants:
 
 
• Individuals who were pathologically confirmed with gastric adenocarcinomas by biopsies without concomitant malignancies and received curative surgeries for gastric cancer.
 
 
Inclusion criteria for non-cancer arm participants:
 
 
• Individuals who showed no signs of cancers based on routine physical examinations, including blood tests, ultrasound and CT, and no sign of gastric cancer from gastric cancer-specific screening tests.
 
 |

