## **6 BASELINE CHARACTERISTICS**

The participants will be adults of 18-85 years with no prior cancer history. The cancer arm will include patients diagnosed with stage I/II gastric cancer. The non-cancer arm will consist of individuals with no known or suspected cancer diagnosis.

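### The cancer-arm criteria do not address therapy before surgery, so a patient downstaged from clinical stage III could be counted as a stage I/II case

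*Protocol*

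**What the plan says.** Protocol, section 5.1 (cancer arm) admits people who were "pathologically confirmed with gastric adenocarcinomas by biopsies without concomitant malignancies and received curative surgeries for gastric cancer". It names no stage and does not mention treatment before the operation.

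Section 5.2 (cancer arm) contains the only eligibility criterion that refers to stage. It excludes "Individuals who were pathologically confirmed with stage III/IV gastric cancer". It does not say which specimen or time point the stage comes from. The synopsis repeats both rules.

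Section 6 describes the arm differently: "The cancer arm will include patients diagnosed with stage I/II gastric cancer". The synopsis likewise plans recruitment in terms of stage I-II patients, and its primary outcome is the AUROC "metric for differentiating stage I/II gastric cancer patients and non-cancer individuals using the cfDNA-based assay".

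On sample timing, section 5.1 (all participants) asks for "Individuals with a plasma sample that was collected before initial screening tests and passed quality control (QC". In section 8, the subsection numbered 7.2 says "A blood sample from each eligible participant will be collected following standard procedures". The Procedure row of the synopsis has blood collected from people with a new diagnosis of cancer.

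**The concern.** According to the synopsis (Sample Enrollment) and subsection 7.2, participants are screened against the inclusion and exclusion criteria. These criteria keep out a patient with stage III disease only if pathology has confirmed that stage. Therapy given between diagnosis and resection can lower the stage found at resection, and no criterion deals with that case.

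The stage label and the blood sample could then describe different disease: the label the tumour after treatment, the plasma the tumour before it. The reported early-stage AUROC and sensitivity would include some cases that had more advanced disease at the draw.

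This would be a bias, so a larger sample would not shrink it. Phase 2 uses the same criteria and could not reveal it. The Phase 1 model and its Youden threshold would also be fitted partly on such cases.

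**Working it through.** The plan states no figure that depends on this point, so there is none to reproduce. The check has two parts: applying the rules to a case, and sizing the possible effect.

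**1. Applying the rules.** Take a patient with biopsy-proven gastric adenocarcinoma at clinical stage III, treated before surgery, then resected with curative intent at pathological stage I or II.

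- Section 5.1, cancer arm: met. Histology was confirmed by biopsy and curative surgery was received.
- Section 5.2, cancer arm: not triggered. Stage III was a clinical finding and was never confirmed by pathology.
- Section 8, subsection 7.3: assigned to the cancer arm, which is defined there by a gastric cancer diagnosis without stage.
- Section 6, read as stage at diagnosis: does not fit the description.

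The criteria admit a patient whom the description in section 6 would leave out.

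**2. Sizing the effect.** Let f be the share of cancer-arm cases that were stage III at the draw. AUROC is an average over cases, so

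observed AUROC = (1 − f) × AUROC(I/II) + f × AUROC(III),

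and the inflation is f × [AUROC(III) − AUROC(I/II)]. Sensitivity at a fixed threshold has the same form.

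The documents give neither f nor performance by stage, so the following are assumptions: f from 2% to 20% (1 to 10 of the ~50 Phase 2 cases), an AUROC gap of 0.02 to 0.10, and a sensitivity gap of 5 to 30 percentage points.

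- AUROC, low end: 0.02 × 0.02 = 0.0004. High end: 0.20 × 0.10 = 0.020.
- Sensitivity, low end: 0.02 × 5 = 0.1 points. High end: 0.20 × 30 = 6 points.
- If f = 0, both are 0.

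A case inside that range, also assumed: sensitivity 75% in true stage I/II and 95% in stage III, AUROC 0.88 and 0.97.

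- f = 10%: sensitivity 0.9 × 75 + 0.1 × 95 = 77%; AUROC 0.9 × 0.88 + 0.1 × 0.97 = 0.889.
- f = 20%: sensitivity 0.8 × 75 + 0.2 × 95 = 79%; AUROC 0.8 × 0.88 + 0.2 × 0.97 = 0.898.

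**3. Scale.** For Phase 2 (~50 cases, ~75 non-cancer), the Hanley-McNeil variance is

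[A(1 − A) + 49(Q₁ − A²) + 74(Q₂ − A²)] / (50 × 75), with Q₁ = A/(2 − A) and Q₂ = 2A²/(1 + A).

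At A = 0.90, Q₁ = 0.8182 and Q₂ = 0.8526. The numerator is 0.090 + 0.401 + 3.155 = 3.646, the variance 3.646/3750 = 0.00097, and the standard error 0.031. At A = 0.80 and 0.95 the standard errors are 0.042 and 0.022. The top of the AUROC range, 0.020, is below all three.

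For sensitivity with 50 cases, √[s(1 − s)/50] is 6.5 points at 70% and 4.2 points at 90%. The 6-point extreme needs a 30-point gap at f = 20%. Stage III sensitivity is then 24 points above the observed value (0.8 × 30), so the observed value cannot exceed 76%. The standard error there is √(0.76 × 0.24/50) = 6.0 points. The extreme is therefore about one standard error, and the 2 to 4 points of the case above are less.

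**The case against.** The strongest reply is that the protocol does state its population. Section 6 refers to stage I/II at diagnosis, and the synopsis plans for stage I-II patients. Read together with section 5.2, these would put a patient diagnosed at stage III outside the arm. This stands in part: it is wrong to say that nothing in the protocol limits the arm to early stage other than the stage found at surgery. But section 6 is descriptive text under Baseline Characteristics, and screening is against the criteria, which do not carry its wording.

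Four further objections stand and limit the point:

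- That stage is read from the resection is an inference from the pathology wording beside the surgery requirement. No section says so.
- The documents neither mention nor exclude therapy before surgery. A reader might infer that such patients are enrolled and that performance is inflated. The text supports only that they can be.
- The upward direction depends on section 5.1, which places the plasma before work-up. The Procedure row of the synopsis and subsection 7.2 allow a later draw. Because cancer-arm eligibility includes having had surgery, subsection 7.2 taken literally puts the draw after the operation. With blood taken after therapy, the effect could vanish or reverse.
- A reader might add patients with no residual tumour at resection. They escape the stage III/IV exclusion, but nothing shows that they would count as stage I/II.

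Training partly on advanced disease need not flatter the assay either; it could lower performance in true early cases.

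Finally, this cannot be left to a statistical analysis plan. Eligibility and the definition of the target condition belong in the protocol.

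**Conclusion.** The point holds as a gap in the eligibility rules, not as a demonstrated bias. The cancer-arm criteria do not address therapy before surgery and do not tie stage to disease before treatment, so a downstaged patient can be labelled stage I/II. They are also out of step with section 6.

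Upward bias in the stage I/II AUROC and sensitivity needs three conditions: such patients enrol, their plasma was drawn before treatment, and stage III is easier to detect than stage I/II. The documents establish none of these as fact; section 5.1 requires the second, but other sections leave it open. The ranges in the working rest wholly on assumed shares and gaps. They describe a modest effect, no larger than about one Phase 2 standard error. It is still worth closing, because the claim is specific to early stage, the second phase would repeat the error, and the correction is cheap.

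**What to change.** In sections 5.1/5.2 and the synopsis, exclude from the cancer arm anyone who received systemic or radiation therapy for gastric cancer before surgery. Pathological stage then reflects untreated disease and, with a pre-operative sample, disease at the blood draw. Align section 6 with the same definition of stage.

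If the investigators prefer to keep such patients, the alternative is one pre-treatment stage definition applied to every case. Staging treated patients clinically and the rest pathologically should be avoided, since it puts two staging bases under one label.

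Separately, reconcile the synopsis (Procedure row), section 5.1 and subsection 7.2 of section 8 on when the sample is drawn. Without that, no stage rule can be matched to the plasma.

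The cost is one eligibility sentence, the matching edits, and a few otherwise eligible cases lost and replaced. Treatment before surgery must be ascertained for each case; the protocol does not say whether it is already recorded. No stated sample size or other figure changes.
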